### Outcome measurements

Since the SPIBI is a multi-professional intervention, the outcome is measured across several domains: outcomes concerning emotional availability in the dyadic relation, outcomes measuring child development and outcomes related to parental mental health and parenthood.

The *primary outcome* is the Emotional Availability Scales (EAS) [65], which will be used primarily at 12 months corrected age but then again at 24 months corrected age. The primary coder is blind to group allocation, whereas the second coder, who is used for interrater reliability checks in 20% of the cases, is not. The scale has four parental dimensions (sensitivity, structure, non-intrusiveness, and non-hostility) and two child dimensions (child responsiveness and child involvement). Each subscale has a maximum score of 29 and a direct score of 1–7. It is hypothesized that higher scores will be observed in the intervention group. Previous international studies have shown significant effects of parental sensitivity and structuring as well as child involvement [50], which also seem to be the subscales most indicative of maternal anxiety in the NICU [66].

The *secondary outcome measurements* are listed below. For measuring the cognitive, language, and motor development of the children, the Bayley Scales of Infant and Toddler Development, Third Edition (BSID-III) [67], will be used at 24 months corrected age. Composite scores are standardized to mean (SD) scores of 100 [15], based on age-matched normative data. The secondary hypothesis is that the mean will be higher in the intervention group.

The child’s executive function at 24 and 36 months corrected age will be measured with the Behaviour Rating of Executive Function, Parental Version (BRIEF-P) [68, 69]. All 5 subscales (*inhibit, shift, emotional control, working memory and plan/organize)* will be used, and the hypothesis is that the intervention group will have fewer executive problems reported.

Child’s motor development will be measured by the Alberta Infant Motor Scale (AIMS) [70, 71] at 3 and 12 months corrected age. The range of the AIMS is 0–58 points, with a hypothesis of higher scores for the intervention group.

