Parental depression will be measured by Hospital Anxiety and Depression Scale (HADS) [72, 73] at term age and at 12, 24 and 36 months corrected age. On the HADS, the range for the depression subscales is 0–21, and the range for the anxiety subscales is 0–21. It is hypothesized that lower scores will be observed for the parents of the children in the intervention group.

Parental anxiety will be measured by the State-Trait Anxiety Inventory (STAI) [74] at term age and at 12, 24 and 36 months corrected age. Both the state and trait scales have a maximum score of 80 points. It is hypothesized that lower scores will be observed for the parents of the children in the intervention group.

Parental self-efficacy will be measured by the Parental Self-Efficacy Scale (PSE) [75] at term age and at 12, 24 and 36 months corrected age. The PSE has 24 items for children at term age and at 12 and 24 months corrected age, while it has 48 items for children of older ages. All items are rated on a 0–10 scale. It is hypothesized that higher scores will be observed for the intervention group at 12, 24 and 36 months corrected age.

Parental resilience will be measured by the Resilience Scale (RES) [76, 77] at term age and at 12, 24 and 36 months corrected age. The RES is a 25-item scale with a 7-point Likert scale. It is hypothesized that higher scores will be observed in the intervention group.

The *other outcome measurements* are listed below. The Hammersmith Neonatal Neurological Outcome (HNNE) is used at term age as a baseline measurement. Post discharge neurological development will be assessed with the Hammersmith Infant Neurological Examination (HINE) [78–80] at 3 months, 12 months, and 24 months corrected age. It is hypothesized that higher scores will be observed for the intervention group. The HINE can be used for infants 2–24 months of age and has optimal scores as well as cut-off values for future less fortunate motor outcomes. It includes 26 items assessing posture, movements, muscle tone, cranial nerve reflexes and reactions, with a score range of 0–3 for each time, thus yielding a possible sum of 0–78 points.

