### Statistical analysis plan

Data will be analysed using intention to treat analysis for the primary outcome and separate testing with multiplicity adjustments for secondary outcomes. Data will be analysed using SPSS version 25 (IBM, New York) and reported according to the CONSORT statement for RCTs. Descriptive parametric statistics will be presented as percentage for categorical variables and as mean and SD for continuous variables such as age or centiles if the data is skewed. Comparisons between the two groups will be performed with Mann-Whitney U test for independent samples. Subgroups with additional analyses will also be used for detaching outcome differences according to number of home-visits in total, additional medical diagnoses and whether one or two parents participated in the intervention. The level of significance is specified at 0.05. To account for repeated measures, to model within-subject variance, and to handle correlated data of continuous variables a linear mixed model will be used. An interaction term will be introduced in the model to examine heterogeneity effect. For binary and ordinal outcome variables Generalized Estimating Equation (GEE) will be employed. For the main analysis no missing data will be imputed. However, classical multiple imputation methods will be used for an additional sensitivity analysis if any of the included variables has more than 5% missing observations. The GEE is a technique which produces unbiased estimates under the assumption that missing observations will be missing at random. An amended approach of weighted GEE will be employed if missingness is found not to be at random. We will perform residual analysis to assess model assumptions and goodness-of-fit.

Generalized linear modelling will be used for outcome variables that are not repeated to create regression models with distribution of the binary and ordinal dependent variables.

The Bonferroni method will be used to appropriately adjust the overall level of significance for multiple comparisons. Count variables will be analyzed using the Poisson regression model. Qualitative variables from the semi-structured interviews will be analysed for their thematic content. The Pearson chi-square test will be used to detect associations between categorical variables, and the mean and standard deviation will be presented for normally distributed continuous variables.

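### The stated 12-month EAS comparison is unadjusted and uses only filmed dyads, so baseline STAI and HADS, already collected and linked to EAS, do nothing to protect it if loss differs by arm

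*Protocol article*

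**What the plan says.** All of the analysis statements are in the Statistical analysis plan section of the protocol article.

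- Principle: "Data will be analysed using intention to treat analysis for the primary outcome".
- Test: "Comparisons between the two groups will be performed with Mann-Whitney U test for independent samples".
- Repeated continuous outcomes: "to handle correlated data of continuous variables a linear mixed model will be used".
- Missing data: "For the main analysis no missing data will be imputed", followed by "classical multiple imputation methods will be used for an additional sensitivity analysis if any of the included variables has more than 5% missing observations".

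The section does not say whether the Mann-Whitney test or the mixed model carries the 12-month EAS result, and it names no baseline covariate for either.

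Under Outcome measurements, EAS is the primary outcome, "which will be used primarily at 12 months corrected age but then again at 24 months corrected age". There is no baseline EAS. The same section says of parental sensitivity, structuring and child involvement: "which also seem to be the subscales most indicative of maternal anxiety in the NICU". STAI and HADS are taken at term age, and the Recruitment section has the baseline questionnaires handed in at the third visit, before randomisation.

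**The concern.** A Mann-Whitney comparison needs an observed EAS value and takes no covariates. With nothing imputed, a randomised dyad that is never filmed at 12 months contributes nothing to it, and the section does not explain how such a dyad stays in an intention-to-treat result.

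The two arms ask different things of families. One has ten visits and two calls over the first year; the other has mainly follow-up assessments. It is plausible, though not shown in the document, that anxious parents leave at different rates by arm. If so, the filmed dyads would differ between arms in baseline anxiety, and through it in EAS, even without any effect of the programme. The two questionnaires that could correct this are on file before allocation.

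If the mixed model is used instead, it keeps a dyad filmed at either visit. A family that leaves during the intervention year has neither film and still adds nothing, so without the baseline scores the same imbalance remains for those families.

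**Working it through.** **The plan's own figure.** Inputs from Sample size and statistical power: 130 dyads allocated 1:1, d = 0.5, alpha 0.05 (taken as two-sided), power 0.8. Normal approximation: 0.5 × √(65/2) − 1.960 = 2.850 − 1.960 = 0.890, and Φ(0.890) = 0.813. The t-test gives 0.808, so the stated power reproduces. The t-test needs 128 observed dyads for 0.80, so 130 leaves almost no room for missing films. The stated effect of 0.5 SD is the yardstick below.

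**Where the bias comes from.** Put EAS and baseline anxiety on SD scales with correlation −r. The unadjusted difference among filmed dyads is then off by

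bias = −r × (mean anxiety of filmed intervention dyads − mean anxiety of filmed control dyads).

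If anxiety drives loss equally in both arms, the bracket is zero and so is the bias, even though loss is then related to EAS within each arm. Bias needs a pattern that differs by arm.

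**Assumed inputs** (the document gives no loss rate and no correlation): no true effect, 65 per arm, r = 0.3 or 0.4, loss of 15% or 25% at average anxiety, 4,000 simulated trials per scenario.

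**Strong difference.** Odds of loss rise 2.7-fold per SD of anxiety in the intervention arm. In control, loss is either flat or reversed. Each cell gives the bias in SD towards SPIBI, then the Mann-Whitney type I error.

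| Control arm | Loss at average anxiety | r = 0.3 | r = 0.4 |
|---|---|---|---|
| flat | 15% | 0.053; 0.052 | 0.065; 0.066 |
| reversed | 15% | 0.094; 0.078 | 0.121; 0.091 |
| flat | 25% | 0.074; 0.061 | 0.096; 0.074 |
| reversed | 25% | 0.148; 0.113 | 0.192; 0.144 |

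Check against the formula, bottom row: 0.148 / 0.3 = 0.49 and 0.192 / 0.4 = 0.48. Both columns imply the same anxiety gap of about half an SD, as they should. Against the planned effect, 0.05 / 0.5 = 10% and 0.19 / 0.5 = 38%.

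**Mild difference.** Odds ratio about 1.5 per SD in the intervention arm, flat in control: bias about 0.02-0.04 SD (4-8% of the planned effect), with type I error close to 0.05.

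**Same pattern in both arms.** Odds ratio 2.7 in both: bias about zero, type I error close to 0.05.

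**Opposite direction.** With a true effect of 0.5 SD and anxiety-driven loss in the control arm only, correlations of 0.2-0.5 pull the unadjusted estimate down to 0.48-0.44 at 10% loss and 0.45-0.40 at 20% loss. Here the bias is against SPIBI.

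**With baseline anxiety in the model and nothing imputed.** In the strong scenarios of the table, a linear model on filmed dyads only, with arm and baseline anxiety, has absolute bias of at most about 0.006 SD and type I error of about 0.04-0.06. In the control-only scenarios it returns the estimate to about 0.50.

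**Precision.** Adjustment scales the standard error by about √(1 − r²): √(1 − 0.09) = 0.954 at r = 0.3 and √(1 − 0.16) = 0.917 at r = 0.4. That is a reduction of about 5% to 8%, somewhat less where the filmed dyads differ in anxiety between arms.

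**The case against.** The strongest reply is that leaving the main analysis without imputation, with multiple imputation as a prespecified check above 5% missing, is a coherent and common plan. That stands. A reader might infer that the no-imputation rule causes the bias and that multiple imputation must become the main analysis. The working does not support this: adjusting for baseline anxiety on observed dyads alone removes the bias. Promoting imputation would be a trade-off, since the headline would then rest on an imputation model.

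Second, the section also names a linear mixed model, which is valid without imputation when loss depends only on what the model contains, and it excludes no covariates. Covariate lists are often left to an analysis plan that is not shown. This stands in part: it cannot be said for certain that the primary result will be a complete-case one. But the only test named for comparing the groups is unadjusted, and no stated EAS analysis uses the baseline scores.

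Third, the larger figures depend on chosen inputs. That also stands. The top values need the highest correlation, the highest loss and opposite patterns in the two arms.

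Two further readings should be resisted. One is that the result is unbiased only if loss is unrelated to EAS within each arm; the equal-pattern case shows otherwise. The other is that the rule lets one blank item delete a whole questionnaire. The document states no item-level rule, scoring is commonly left to the instrument manual or analysis plan, and EAS is coded from video.

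**Conclusion.** The point holds as a missed protection, not as proof of a biased trial. As written, the group comparison of 12-month EAS drops unfilmed dyads and ignores two baseline scores that are in hand and that the article's own text ties to EAS. The bias is nil if loss follows anxiety in the same way in both arms, about 0.02-0.04 SD for a mild arm difference, and 0.05-0.19 SD for strong ones; its direction depends on which arm loses the anxious parents. These sizes rest on assumed correlations of 0.3-0.4 and loss of 15-25% at average anxiety. They also assume that loss is explained by measured baseline anxiety: adjustment does not cure loss driven by things not recorded. Because adjustment also tends to sharpen the estimate, it is worth making whether or not the feared pattern occurs.

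**What to change.** Name the primary 12-month EAS analysis: a linear mixed model of EAS at 12 and 24 months with arm, visit, arm by visit, and baseline STAI and HADS, reporting the arm difference at 12 months. Make Mann-Whitney a supporting analysis. State that dyads with no film at either visit add no EAS value and that the result relies on loss being explained by arm, the baseline scores and the observed EAS. This is consistent with imputing no missing outcomes in the main analysis.

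Keep multiple imputation as the sensitivity analysis and list baseline STAI and HADS among its predictors.

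The cost is a short edit to the section, with no new data. Three details must be fixed before unmasking: which STAI and HADS subscales enter, whose scores are used when two parents answer, and what happens to a dyad whose baseline form is missing. The effect becomes an adjusted mean difference and so leans on the model's residual assumptions, which the plan already intends to check.

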### Trial design

The SPIBI trial is a two-arm randomized trial with four recruiting sites in Stockholm. The intervention group (IG) receives 10 visits and two telephone calls from a special trained interventionist (see Table 3). The focus of the intervention is providing strengths-based support of the parent-child interaction, sensitizing parents to infant cues, helping the parent to give optimal developmental support to the infant and enhancing the infant’s self-regulating skills. All extremely preterm children in Stockholm are routinely offered an extensive follow-up test programme, and SPIBI participants are subject to additional assessments at 3 months, 12 months, and 24 months corrected age. Additionally, the children’s preschool teachers will be interviewed when they reach 36 months corrected age. Control participants will have an additional meeting with the project coordinator when they are informed that they have been allocated to the control group, in which information will be provided about the discharge process, their child’s behavioural cues and the importance of parent-child interaction at home. The trial began on 1 September 2018, and recruitment is anticipated to end on 31 August 2020 or at a later date when the target 130 is reached. The intervention will continue for 1 year after the last participant has been included.

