### Sample size and statistical power

The hospitals in Stockholm treat more than 100 extremely preterm infants every year, but several of them are not residents of Stockholm County, which is a prerequisite for study inclusion. The study team is prepared to recruit 130 participants, 50% of which will be randomized to the SPIBI intervention. The sample size is based on feasibility, and the assumption is that the effect size of the intervention on the primary outcome measure Emotional Availability Scales (EAS) will be moderate, i.e., Cohen’s d = 0.5. This is largely in line with the results of Flierman et al. [50] for the sensitivity scale of the EAS in the previously mentioned Dutch trial. Hence, we aim to recruit 130 participants, which gives us a power of 0.8 given a normal distribution and an alpha value of 0.05.

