### Recruitment and randomization

#### Recruitment

The PhD student working with the project spends 8–20 h per week as a project coordinator (see Table 3) visiting the four neonatal units and two medical child wards to identify families eligible for recruitment. The standard procedure for recruitment includes three visits. The first visit takes place during GW 32–36 and aims to provide initial information about the discharge process in general, including the neonatal follow-up programme and the SPIBI project in particular. This initial visit is only implemented if the nurse or neonatologist in charge of the child considers the patient to be medically stable. Two days to three weeks later, a second visit will take place, during which parental questions are answered and the intervention programme as well as the conditions for participating in an RCT are explained in detail. It is stressed that research participation is voluntary and that the family may withdraw from the project at any time with no further consequences. Participating parents are given a three-page information sheet and a consent form to sign, as well as four baseline assessment questionnaires. During the third visit, informed consent and baseline questionnaires are collected, and information about the project is repeated if necessary. The participant is randomized, and if assigned to the control group, a fourth visit is needed to provide information about this circumstance, as well as the fact that the child and parents are now a part of an extended follow-up starting at 3 months corrected age, and at 1 year corrected age, the PhD student will see the family again for assessment and a follow-up interview. If the participant is assigned to the intervention group, the assigned interventionist will visit the family as soon as possible.

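### The stated sensitivity analysis for missing continuous EAS data stays within missing at random, so it cannot test dropout that depends on the unseen 12-month score

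*Protocol article*

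**What the plan says.** All text on missing data is in the protocol article, Statistical analysis plan. Four statements matter.

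- The main analysis uses observed data: "For the main analysis no missing data will be imputed".
- One further check is stated: "classical multiple imputation methods will be used for an additional sensitivity analysis if any of the included variables has more than 5% missing observations".
- Missingness found not to be at random is to be met with weighted GEE. The same section assigns GEE to binary and ordinal outcomes and a linear mixed model to repeated continuous ones.
- A Mann-Whitney U test is named for comparing the two groups. The section does not say whether this test or the mixed model is the primary EAS analysis.

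Under Outcome measurements, EAS is measured at 12 months corrected age (primary) and again at 24 months. No baseline EAS is described. Sample size and statistical power treats EAS as a normal variable whose effect "will be moderate, i.e., Cohen’s d = 0.5".

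**The concern.** A sensitivity analysis for missing data should vary the assumption on which the main result rests. A likelihood-based mixed model and classical multiple imputation are both valid under missing at random: given what was observed, the missing EAS values follow the same distribution as the observed ones. Agreement between the two says nothing about dropout that depends on the 12-month EAS itself.

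Such dropout is plausible here, and its causes could differ by arm. Under Recruitment, "the family may withdraw from the project at any time with no further consequences". Under Trial design, "The intervention group (IG) receives 10 visits and two telephone calls from a special trained interventionist". Home visits 4 to 9 fall between 3 and 12 months, whereas the study contacts described for control families are at 3 months and then at 12 months. Without a baseline EAS, a dyad lost before 12 months that does not return contributes no EAS value on which a model could condition.

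If SPIBI families with poorer interaction were the ones to leave, the main analysis would favour SPIBI and the planned check would lean the same way. Readers could then take their agreement as evidence of robustness.

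**Working it through.** **1. The plan's own figure.** Inputs from Sample size and statistical power: "Hence, we aim to recruit 130 participants", "50% of which will be randomized to the SPIBI intervention", d = 0.5, and the claim "which gives us a power of 0.8 given a normal distribution and an alpha value of 0.05". Two-sided testing is assumed. With 65 per arm the normal approximation gives

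power = Φ(0.5 × √(65/2) − 1.96) = Φ(2.850 − 1.96) = Φ(0.890) = 0.813.

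The t-test gives 0.808. The stated 0.8 is reproduced, and it treats EAS as continuous and normal.

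**2. Bias when only the missing SPIBI dyads score lower.** Assumptions, none from the document: no true effect, a fraction f of EAS-12 missing in each arm, control losses at random, and missing SPIBI dyads δ SD below the observed ones. The full SPIBI mean equals the observed mean minus f × δ, so completers overstate the effect by f × δ. With m = 65 × (1 − f) observed per arm, SE = √(2/m), and the two-sided error rate is Φ(−1.96 + fδ/SE) + Φ(−1.96 − fδ/SE).

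| f | m | SE | δ | Bias f × δ (SD) | False-positive rate |
|---|---|---|---|---|---|
| 0.15 | 55.25 | 0.190 | 0.5 | 0.075 | 0.07 |
| 0.15 | 55.25 | 0.190 | 1.0 | 0.15 | 0.12 |
| 0.20 | 52 | 0.196 | 0.5 | 0.10 | 0.08 |
| 0.20 | 52 | 0.196 | 1.0 | 0.20 | 0.18 |

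A simulation of the same four scenarios (3000 trials each) gave completer biases of 0.07, 0.15, 0.10 and 0.19, and error rates after missing-at-random imputation of 0.07, 0.13, 0.08 and 0.18.

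**3. What multiple imputation does to that bias.** In a second simulation there was no true effect, about 20% were missing, SPIBI loss depended on the unseen EAS-12, and missing SPIBI dyads were about 1 SD lower. The estimates depend on what the imputation model can use:

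| Auxiliary data (assumed correlation with EAS-12) | Completers | After imputation |
|---|---|---|
| none | +0.19 | +0.19 |
| EAS-24 (0.5) | +0.19 | +0.15 |
| EAS-24 (0.5) and a baseline score (0.4) | +0.19 | +0.13 |
| EAS-24 (0.7) | +0.19 | +0.10 |

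A repeat with a slightly stronger loss mechanism started at +0.23 for completers and gave +0.23, +0.18, +0.16 and about +0.13 after imputation, the same pattern. The gains require EAS-24 to be observed in dyads that missed EAS-12. Imputation reduced the bias and never removed it.

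**4. What a shifted analysis would show.** Suppose the missing-at-random estimate is 0.5 and only the missing SPIBI values are shifted. Significance is lost when the shift exceeds (0.5 − 1.96 × √(2/m)) / f, with the SE held fixed.

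| f | 1.96 × SE | Shift at which significance is lost (SD) |
|---|---|---|
| 0.05 | 0.353 | 2.95 |
| 0.10 | 0.362 | 1.38 |
| 0.15 | 0.373 | 0.85 |
| 0.20 | 0.384 | 0.58 |
| 0.30 | 0.411 | 0.30 |

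At 5-10% loss a result of the planned size is secure against shifts up to 1 SD. At 15-20% it is not.

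**The case against.** Several stronger readings are tempting, and the document does not support them.

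- *The plan ignores missingness that is not at random.* It does not: it names weighted GEE for that case. The remedy is, however, written for binary and ordinal outcomes. It also ordinarily needs missing at random itself, since the weights are estimated from observed data, and observed data alone cannot establish that missingness is not at random. The 1-7 direct scores could be analysed as ordinal, which would bring EAS under GEE, but the power statement points to a continuous analysis.
- *The check repeats the assumption of the main analysis and must reproduce its result.* This is not established. If the main test is Mann-Whitney on complete cases, imputation relaxes a stricter assumption and is useful. It can also draw on EAS-24, on parent questionnaires at term age and on 3-month child assessments, and step 3 shows that this can move the estimate.
- *The check says nothing about dropout at all.* It can show whether dropout related to observed data matters. The gap concerns only dropout that depends on the unseen EAS.
- *The 5% trigger is a defect of its own.* It is not. It counts EAS among the variables, it would fire at the loss assumed here, and at 5% loss a shift of about 2.95 SD would be needed to overturn d = 0.5.

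It is also fair to say that the loss rate, the one-arm mechanism and its direction are assumptions, that with a 0.5 SD gap the error rate rises only to 0.07-0.08, and that a fuller analysis plan may add a further check. The point rests on the method that the article commits to, not on a detail that it leaves out.

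**Conclusion.** The concern holds in a limited form. For EAS analysed as continuous, the stated sensitivity analysis stays within missing at random, and the provision for missingness that is not at random is tied to other outcome types. The planned check therefore cannot show whether dropout that depends on the unseen 12-month EAS drives the primary result.

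Under the assumed 15-20% loss and a 0.5-1 SD deficit in missing SPIBI dyads only, the bias is about 0.07-0.20 SD before any gain from auxiliary variables, or 15% to 40% of the planned effect (0.075/0.5 and 0.20/0.5). These figures illustrate the risk and do not predict it. The document gives no loss rate and does not suggest that loss will favour SPIBI. The change is a worthwhile and cheap improvement; nothing here shows the planned main analysis to be invalid.

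**What to change.** For EAS at 12 months:

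1. Keep multiple imputation under missing at random, with arm, EAS-24 and the baseline parent scores in the imputation model, as the zero-shift case.
2. Add a delta adjustment: shift the imputed values separately by arm, for example from 0 to -1 SD in steps of 0.25 SD.
3. Report the shift, or pair of shifts, at which the primary conclusion changes, beside the observed loss in each arm.

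This needs no new data, only a few sentences in the analysis plan and a few hours of programming, since a constant is added after imputation. It should be fixed before the 12-month data are analysed by arm. The downside is one extra table, and a positive result may have to be reported as fragile.

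### The missing-data rule for GEE is misstated: unweighted GEE is not in general unbiased under missing at random, and weighted GEE does not correct data missing not at random (repeated binary and ordinal outcomes only)

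*Protocol article*

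**What the plan says.** All of this is in the protocol article, section Statistical analysis plan.

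- Choice of model: "For binary and ordinal outcome variables Generalized Estimating Equation (GEE) will be employed". For repeated continuous outcomes, "to handle correlated data of continuous variables a linear mixed model will be used". Outcomes measured once go to generalized linear modelling.
- Handling of gaps: "For the main analysis no missing data will be imputed". As a supplement, "classical multiple imputation methods will be used for an additional sensitivity analysis if any of the included variables has more than 5% missing observations".
- Justification: "The GEE is a technique which produces unbiased estimates under the assumption that missing observations will be missing at random".
- Fallback: "An amended approach of weighted GEE will be employed if missingness is found not to be at random".

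The section does not list which outcomes will be analysed by GEE.

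**The concern.** The last two statements form a decision rule: keep unweighted GEE if data are missing at random, and move to weighted GEE if they are not. Each half pairs a method with an assumption it does not match.

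| Missingness | Article's rule | What the method needs |
|---|---|---|
| Completely at random, or dependent on model covariates only | unweighted GEE | valid |
| At random (may depend on earlier observed outcomes) | unweighted GEE | can be biased; weighting with a correct dropout model is valid |
| Not at random (depends on the unseen value) | weighted GEE | still biased |

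The trigger is a further problem. At random and not at random differ only in how missingness relates to values nobody observed, so no test on the collected data separates them. Whoever applies the rule would be choosing between estimators, after seeing data, on a criterion that the data cannot settle.

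Follow-up runs to 36 months corrected age and only one arm receives the home visits. Dropout related to earlier outcomes and differing by arm is therefore plausible, although the article gives no dropout figures.

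**Working it through.** **The plan's own figure.** The only reproducible figure nearby is the power of 0.8 with 130 participants, for an effect that "will be moderate, i.e., Cohen’s d = 0.5" and "The level of significance is specified at 0.05" (two-sided assumed). With 65 per arm, power = Φ(0.5·√(65/2) − 1.96) = Φ(0.89) = 0.81. It reproduces, and nothing below depends on it.

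**Check 1: two visits, true odds ratio 1.00.** All inputs are assumptions. The event rate is 0.35 in both arms at both visits, and the within-child latent correlation is 0.7. Second-visit dropout is 40% in controls with an event at visit 1 and 10% in everyone else.

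1. A bivariate normal with correlation 0.7, cut at 0.35, gives P(event at both) = 0.233 and P(event at visit 2 only) = 0.117.
2. Controls retained: 0.6 × 0.35 + 0.9 × 0.65 = 0.795.
3. Observed control rate: (0.6 × 0.233 + 0.9 × 0.117) / 0.795 = 0.308. In the intervention arm dropout is unrelated to outcome, so the rate stays at 0.35.
4. Unweighted GEE with independence working correlation and an arm-by-visit term reproduces the observed rates: (0.35/0.65) / (0.308/0.692) = 1.21. Large simulations of the same set-up gave 1.18 to 1.21.
5. Weighting each retained control by the inverse of its retention probability: 0.6 × 0.233/0.6 + 0.9 × 0.117/0.9 = 0.35. The odds ratio returns to 1.00.
6. An exchangeable working correlation, which fits these data, gave 0.99 to 1.00.

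Range over the assumed 40%, by the same steps: dropout of 20%, 30%, 40% and 50% in that stratum gives odds ratios of 1.06, 1.13, 1.21 and 1.31. With 10% throughout, it is 1.00.

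**Scale at the trial's size.** With 65 per arm, about 51.7 controls and 58.5 intervention children are retained. The standard error of the log odds ratio is √[1/(51.7 × 0.308 × 0.692) + 1/(58.5 × 0.35 × 0.65)] = 0.41. The bias is ln 1.21 = 0.19, or 0.46 standard errors. The two-sided false-positive rate becomes Φ(−1.96 + 0.46) + Φ(−1.96 − 0.46), about 7.5% instead of 5%.

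**Check 2: three visits, monotone dropout, 100,000 simulated children with a shared random intercept.** Inputs are again assumed. Retention per visit is 0.8 throughout (completely at random), or about 0.88 except 0.5 for intervention children with an event at the previous visit (at random) or at the current visit (not at random). Entries are arm log odds ratios at visit 3.

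| Mechanism | Full data | Unweighted, independence | Weighted |
|---|---|---|---|
| Completely at random | −0.46 | −0.47 | −0.47 |
| At random | −0.51 | −0.91 | −0.50 |
| Not at random | −0.48 | −1.26 | −1.12 |

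Weighting removes the error under missing at random. Under missing not at random it removes only 0.14 of an error of 0.78.

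Unweighted exchangeable GEE was fitted on a subset of 30,000. Under missing at random it gave −0.49 against −0.50 where the structure fitted. With serially dependent data, where it did not fit, it was off by about 0.05 to 0.10. Under missing not at random it stayed clearly biased, at about −1.0 to −1.1.

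**The case against.** Several points on the other side have weight.

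- **Reach is narrow.** The listed secondary outcomes are scale scores, and repeated continuous scores go to the linear mixed model. The General Movement Assessment and the M-CHAT are each measured once. Candidates for GEE are the ICF-CY items, the HINE if it is cut at its thresholds, or the EAS 1–7 direct score if treated as ordinal; the article assigns none of them. A reader might infer that the primary outcome is affected, but the document does not support that. This point stands and lowers the severity.
- **The bias depends on the working correlation.** A reader might infer that the planned GEE is certainly biased. It is not: a structure that fits leaves little or no bias in these examples. The article names none, but that is a detail it may leave to a fuller plan and is not a fault here. This stands, so the supportable wording is that the estimate can be biased.
- **Multiple imputation is already planned above 5% missing.** In Check 1 the missing share is 20.5% in controls and 10% in the intervention arm, so it would be triggered and would give a comparison valid under missing at random if the imputation model is adequate. This is real mitigation, but only as a sensitivity analysis, and as usually applied it does not address missing not at random.
- **No imputation in the main analysis might look like an error.** By itself it is not, since a likelihood-based mixed model is valid under missing at random without it.
- **The wording may be a slip.** If at random was meant as completely at random, the rule is close to conventional and its trigger is partly testable. The article does not say so, and a rule that is right only when a standard term is misread still needs correcting.

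**Conclusion.** The two sentences are wrong as written. This is a stated rule and not a detail left to another document. Unweighted GEE does not in general deliver unbiasedness under missing at random, weighted GEE does not rescue data missing not at random, and the switch between them has no testable trigger. The finding is confined to repeated binary and ordinal outcomes. It does not touch the sample size and is not shown to touch the primary EAS analysis.

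The size is conditional. An odds ratio of about 1.2 against a true 1.00 needs independence working correlation and 40% against 10% dropout concentrated in one arm's event stratum; milder dropout gives less, and a well-fitting exchangeable structure gives about none. The direction of any bias in the trial cannot be predicted from the document. Severity is moderate: it should be corrected because it decides which estimator is reported, but it does not undermine the trial's main conclusion.

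**What to change.** Replace the two sentences as follows.

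1. State that unweighted GEE assumes data missing completely at random or missingness that depends only on model covariates.
2. For repeated binary or ordinal outcomes, make the main analysis under missing at random either inverse-probability-weighted GEE, with the dropout model specified in advance (for example arm and earlier outcomes), or multiple imputation followed by GEE. Both keep the marginal treatment effect. Imputation copes more easily with visits missed intermittently. A generalised linear mixed model is not a like-for-like substitute, because its effect is subject-specific. If imputation is chosen, the statement that the main analysis uses none must be limited to the other outcomes.
3. Delete the rule that switches method according to what missingness is found to be.
4. Do not describe weighted GEE as a remedy for data missing not at random. Examine that case by a sensitivity analysis such as delta-adjusted multiple imputation with shifts by arm, which extends the imputation already planned.

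The cost is wording, some programming (including a check that the named software can fit the chosen method) and slightly wider intervals from weighting. No new data are needed and the sample size is unchanged.
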